## Abstract

**Background:**

Many patients with chronic heart failure (CHF), a common condition with high morbidity and mortality rates, receive treatment in primary care. To improve the management of CHF in primary care, we developed an implementation programme comprised of educational and organisational components, with support by a practice visitor and focus both on drug treatment and lifestyle advice, and on organisation of care within the practice and collaboration with other healthcare providers. Tailoring has been shown to improve the success of implementation programmes, but little is known about what would be best methods for tailoring, specifically with respect to CHF in primary care.

**Methods/design:**

We describe the study protocol of a cluster randomised controlled trial to examine the effectiveness of tailoring a CHF implementation programme to general practices compared to a standardised way of delivering a programme. The study population will consist of 60 general practitioners (GPs) and the CHF patients they include. GPs are randomised in blocks of four, stratified according to practice size. With a tailored implementation programme GPs prioritise the issues that will form the bases of the support for the practice visits. These may comprise several issues, both educational and organizational.

The primary outcome measures are patient's experience of receiving structured primary care for CHF (PACIC, a questionnaire related to the Chronic Care Model), patients' health-related utilities (EQ-5D), and drugs prescriptions using the guideline adherence index. Patients being clustered in practices, multilevel regression analyses will be used to explore the effect of practice size and type of intervention programme. In addition we will examine both changes within groups and differences at follow-up between groups with respect to drug dosages and advice on lifestyle issues. Furthermore, in interviews the feasibility of the programme and goal attainment, organisational changes in CHF care, and formalised cooperation with other disciplines will be assessed.

**Discussion:**

In the tailoring of the programme we will present the GPs a list with barriers; GPs will assess relevance and possibility to solve these barriers. The list is rigorously developed and tested in various projects. The factors for ordering the barriers are related to the innovation, the healthcare professional, the patient, and the context.

CHF patients do not form a homogeneous group. Subgroup analyses will be performed based on the distinction between systolic CHF and CHF with preserved left ventricular function (diastolic CHF).

**Trial registration:**

ISRCTN: ISRCTN18812755

## Background

Chronic heart failure (CHF) is a highly prevalent chronic disease with high morbidity and mortality rates. The prevalence of CHF in the Western world is 1% to 2% in the general population and at least 10% among the age group of 85 years and older [1,2]. Mortality in CHF patients is high compared to their age group [2,3]. High morbidity is associated with high hospital admission rates and reduced quality of life [4]. There are effective, evidence-based treatments which improve mortality and morbidity but use of and adherence of treatments is suboptimal despite clinical guidelines [5-9].

A large group of patients with CHF receive treatment in primary care. There are many programmes for the management of long-term conditions in primary care -- *e.g*., diabetes, COPD and depression -- but at present not for CHF, though several disease management programmes exist for CHF related to outpatient clinics. As a substantial proportion of CHF patients do not attend such clinics but visit their GP instead, these patients are not enrolled in a structured care programme.

To improve the management of CHF in primary care, we have developed an implementation programme, comprising both educational and organisational components, the latter aimed at improved and structured care. We pilot tested this programme in 19 general practices [10]. The pilot programme was targeted at implementing the prevailing practice guideline for general practice [11]. In the mean time, in the Netherlands an interdisciplinary guideline on CHF, based on the European Society of Cardiology (ESC) guideline, was developed and published in May 2010 [12]. So, we adapted the implementation programme according to this new guideline, taking into account the lessons learned in the pilot study.

Apart from offering a standard implementation programme, another approach is to tailor an intervention to the special needs and conditions in a general practice. Ideally, tailoring has three components: identification of factors associated with implementation (or labelled as 'barriers to change'), to match implementation interventions to those factors, and evaluation of the tailored implementation programme. Tailoring has been shown to have a modest effect on the success of the implementation programme [13], but little is known about what would be best methods for tailoring [14]. In addition, research evidence specifically supporting this hypothesis with respect to improving primary care for CHF patients is not yet available. In one study no relation was found between barriers perceived and ACE inhibitor prescription behaviour [15]. Earlier studies to improve CHF patients care focused on disease management programmes, mainly case management, and on education and drug prescription [16,17].

Patients being clustered in practices, we planned to conduct a cluster randomised controlled trial with randomisation at the practice level. The aim of the study will be to examine the effectiveness of tailoring the implementation programme to general practices compared to a standardised way of delivering the implementation programme to general practices.

## Methods

The project will be a collaborative project of IQ healthcare, a research department of Radboud University Nijmegen Medical Centre, and the four regional supportive structures for primary care ('ROS') in the south of the Netherlands and their cooperative bond Robuust. The medical ethical committee (CMO Regio Arnhem -- Nijmegen) assessed the study proposal and waived approval.

### Participants

The study population will consist of 60 general practitioners (GPs) and the CHF patients they will include. GPs will be recruited in the south of the Netherlands, contacted either directly or indirectly via various regional organisations by advisors of the regional supportive structures for primary care. GPs will be informed about the project, and when they agree to participate they will be instructed to send in an admission form with data on practice organization necessary for stratification and randomization.

Evidence of change will be assessed by studying the effects of the intervention on patients with CHF registered with the participating GPs. As in the pilot [10], GPs will include all CHF patients from their practices who are over 18 years of age of whom the GPs consider themselves to be the physician taking care of the treatment of this condition in the patient. We expect eight to ten patients per practice [18,19]. Patients will be sent explanation about the study and asked for informed consent to participate in a patient questionnaire. Data collection will be anonymized.

## Interventions

### Standardised delivery of the implementation programme

The implementation pack contains educational materials for the professionals and patients. There is a recommended protocol for multidisciplinary management and a template for clinical care presented as a guiding registration form. Furthermore, we offer support by a visiting practice consultant and the possibility to contact a GP with a special interest in CHF management.

The project materials from the pilot were amended following the pilot study and the development of the new interdisciplinary practice guideline [12]. Participating GPs will be informed about healthcare professionals from other primary care disciplines, *e.g*., dieticians and physiotherapists, and these professionals will be informed about the project, encouraging the role of the multidisciplinary team in CHF management. The paragraph on non-pharmaceutical treatment was enlarged and the pharmaceutical paragraph had some changes. Now, recommendations on drug treatment are different for patients with systolic CHF compared to patients with a preserved systolic heart function, so called diastolic CHF (See Table 1). Finally, new recommendations on the use of devices were formulated.

**Table 1 T1:** Changes in medication advice

Medication advice based on the 2005 GP practice guideline	Medication advice based on the 2010 multidisciplinary guideline
One scheme:	Systolic heart failure:
- Diuretics	- ACE inhibitor (or ARB if not tolerated) in evidence based doses
- ACE inhibitors or ARB	- Diuretics for fluid retention
- Beta blocker	- Beta blocker blockers licensed for heart failure in evidence based doses
- Aldosteron antagonist	- Aldosterone antagonist or ARB
- Digoxin	- Digoxin or H + ISND
	
	Diastolic heart failure:
	- Diuretic if signs of fluid retention
	- Adequate treatment of co morbidity
	- Strict blood pressure control

ARB = angiotensin II receptor blocker

H + ISDN = Hydralazine + isosorbide dinitrate

The paper template is used to direct care and collect data to demonstrate the effectiveness of the interventions. Demographic data is collected in particular the aetiology of the CHF and the diagnostic category, whether diagnosis was echocardiography based, on the existence of diastolic or systolic CHF, and pharmaceutical treatment at the start of the project period. A second page poses questions about non-pharmaceutical issues such as advice about physical activity and influenza vaccination. Finally, we offer different forms for patients with systolic or diastolic CHF, based on the recommendations on medication as summarised in Table 1.

The pilot study demonstrated that three practice visits was the optimum number and these shall be offered to all participating practices. The practice visitor is an educational facilitator trained in supporting behaviour change in practices.

The pilot study also demonstrated that there was little multidisciplinary clinical activity in the improvement of care for CHF patients, and this has been addressed in this project. We now use the multidisciplinary practice guideline as a starting point instead of the monodisciplinary GP's practice guideline. Furthermore, the regional advisors will determine the social network in the practice area, providing information on other primary care disciplines, *e.g*., dieticians and physiotherapists, with extra expertise and interest in CHF treatment. These workers in the other disciplines will be informed about the project and receive relevant information in line with the multidisciplinary guideline.

All materials are offered paper based in a binder. We will also present all materials on a website and examine the possibilities for designing the guiding patient registration forms on this website as well.

### Tailored delivery of the implementation intervention

The intervention group of practices will have the agenda of their practice visits determined by the results of a questionnaire identifying the barriers they perceive to the introduction of a programme for the management of CHF in primary care. The barriers listed in the questionnaire are based on previous research and grouped in relation to the innovation, the healthcare professional, the patient, and the context [20]. GPs are asked to indicate the relevance of each barrier in their practice situation on a five-point scale, and whether or not they think that the barrier can be solved. Table 2 shows some examples of barriers suggested in the format of the questionnaire. GPs are offered the possibility to add barriers they perceive that are not yet identified. When barriers are identified, those that are relevant and solvable will be prioritised and addressed during the practice visits.

**Table 2 T2:** Examples of possible barriers as presented in the GP's questionnaire for the tailored intervention.

		To what extend is this barrier relevant for your practice situation?	Do you consider it possible to solve this barrier in your practice situation?
1.	**Innovation**		

	The recommendations in the multidisciplinary practice guideline heart failure ask for changes in our existing practice routines that are too big.	❑ Not at all ❑ A little ❑ Neutral ❑ Relevant ❑ Very relevant	❑ Yes ❑ No ❑ Doubtful

2.	**Health care professional**		

	I lack sufficient knowledge of the recommendations in the multidisciplinary practice guideline heart failure.	❑ Not at all ❑ A little ❑ Neutral ❑ Relevant ❑ Very relevant	❑ Yes ❑ No ❑ Doubtful

3.	**Patient**		

	Considering patients with complex health issues all time reserved usually is taken completely by the actual problems and we do not manage to provide a more structured approach for the heart failure problems.	❑ Not at all ❑ A little ❑ Neutral ❑ Relevant ❑ Very relevant	❑ Yes ❑ No ❑ Doubtful

4.	**Context**		

	We lack sufficient supportive staff to provide care according to the practice guideline.	❑ Not at all ❑ A little ❑ Neutral ❑ Relevant ❑ Very relevant	❑ Yes ❑ No ❑ Doubtful

### Objectives

The objective of the study is to examine the effectiveness of identifying barriers to change, and tailoring education and support in comparison with a standard intervention programme, to improve the management of patients with CHFin primary care.

Our null hypothesis is that tailoring does not result in better implementation of the guidelines for CHF compared to a standardised delivery of our implementation programme. In addition, we will also examine whether either of the two programmes are associated with improvements in healthcare delivery and patient outcomes.

### Measures

Data collection will comprise the following measures: patient questionnaires, patient registration forms, and telephone interviews with the GPs. Practices will send out patient questionnaires based on validated and previous used questionnaires: PACIC [21], EQ-5D [22], questions about 'continuity of care,' and Morisky's questionnaire on medication adherence [23]. In the patient registration forms, data about non-pharmaceutical and drug therapy are registered by the GPs and their staff: they register the baseline treatment at inclusion, and during the patient contacts throughout the study period they register all advice given, referrals, drug therapy changes, and information on hospitalisation and mortality. The GP interview will score goal attainment and a qualitative assessment of the programme. All measures have been applied by our group in previous studies.

### Outcomes

The primary outcome measures are determined at the patients' level and consist of experience of receiving structured primary care for CHF (PACIC) and health-related utilities (EQ-5D), and of drug prescriptions.

PACIC is a questionnaire consisting of 27 items, which is related to the Chronic Care Model [24]. We translated and validated PACIC for use in general practice in the Netherlands [25]. EQ-5D consists of five questions and a Visual Analogue Scale (VAS), which has been validated for use in the Netherlands [26]. These outcome measures reflect key aspects of medical treatment, organization of care, and patient reported quality of life, and were chosen pragmatically because of the availability of relevant, validated, responsive, composite measures.

Drug prescription scores are assessed using the guideline adherence index (GAI), indicating the proportion of indicated drugs that is prescribed [27,28]. These include ACE inhibitors and beta blockers, and -- depending on the patient's CHF severity according to the NYHA classes -- further drug classes [12].

Secondary outcome measures at the patients' level concern lifestyle advice and medication during the study period, based on the patient registration forms providing information on non-pharmaceutical advice and drug prescriptions, continuity of care, and medication adherence. Considering drug therapy we will assess the percentages of ACE inhibitors and beta blockers prescribed in the evidence-based target dosages. Secondary outcome measures at the practice level are goal attainment and qualitative assessment of the programme, focussing on the subjective GP's experiences, for instance on improvement of practice organisation and collaboration with other primary care professionals.

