### Data analysis

The primary analysis is a comparison of primary outcomes at follow-up between the study groups, taking into account clustering of patients within practices. Multilevel regression analyses will be used to explore the effect of practice size and type of intervention programme. In addition, we will examine both changes within groups and differences at follow-up between groups with respect to percentage of patients on the maximum tolerated dosage of ACE inhibitor or angiotensin II receptor blocker and of beta blockage; medication completely according to the guideline; having received influenza vaccination in the winter season 2010-2011; having received professionally guided physical activity training; and the number of non-pharmaceutical issues addressed. If possible, subgroup analyses will comprise type of CHF (systolic or diastolic) and diagnostic certainty (secondary care diagnosis, echocardiography diagnosis) The interviews will be used to assess the feasibility of the programme and goal attainment, organisational changes in CHF care, and formalised cooperation with other primary care disciplines and specialist care.

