### Sample size

Power calculations are based on the primary outcome measurement PACIC. The PACIC comprises 27 questions with an answering scale from 1 to 5. A previous unreported study showed that its standard deviation was 1.0. To detect a difference of 0.3 points with a standard deviation of 1 (a relatively small effect), with alpha = 0.05 and beta = 0.20, ICC = 0.05, a total of 51 practices with 10 patients each would be required, or 59 practices with 8 patients.

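### Three equal primary outcomes face one null hypothesis with no success rule, while the alpha and sample size fit a test of PACIC alone

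*Protocol article*

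**What the plan says.** The Outcomes section lists as primary "experience of receiving structured primary care for CHF (PACIC) and health-related utilities (EQ-5D), and of drug prescriptions". The abstract repeats the three, and the Discussion states again that drug prescription counts as primary. None is ranked above another.

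The Objectives section gives one null hypothesis: "Our null hypothesis is that tailoring does not result in better implementation of the guidelines for CHF", compared with standardised delivery. A separate sentence there adds the question whether either programme is associated with better care delivery and patient outcomes.

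The Data analysis section says "The primary analysis is a comparison of primary outcomes at follow-up between the study groups", allowing for clustering. It gives no order, no division of alpha, and no statement whether one, two or all three outcomes must be positive.

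The Sample size section says "Power calculations are based on the primary outcome measurement PACIC". The inputs are "To detect a difference of 0.3 points with a standard deviation of 1", "with alpha = 0.05 and beta = 0.20, ICC = 0.05", and the result is "a total of 51 practices with 10 patients each would be required, or 59 practices with 8 patients". This is the only alpha in the article. Sidedness is not stated.

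**The concern.** These statements do not fit together. Three outcomes of equal rank imply a family of three tests. One null hypothesis implies one decision. The alpha and the sample size imply that PACIC alone makes that decision.

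If PACIC is positive and GAI is not, or the reverse, the text does not say whether the null hypothesis is rejected, so the choice could be made after the results are known. The 5% error rate would then not apply to the conclusion drawn.

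EQ-5D adds a second mismatch. It measures patient health, whereas the null hypothesis concerns implementation of guidelines. It is nevertheless an equal primary outcome. Neither EQ-5D nor GAI has any stated power.

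**Working it through.** **Inputs.** From Sample size: difference 0.3, SD 1, alpha 0.05, power 0.80, ICC 0.05, and 10 or 8 patients per practice. From Participants: 60 GPs, taken here as 60 practices. Allocation is assumed 1:1 (two groups, blocks of four).

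**1. Reproduce the stated size.** Patients per arm before clustering: 2 × ((1.960 + 0.842)/0.3)² = 174.4. The design effect is 1 + (m − 1) × 0.05.

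- m = 10: design effect 1.45; 2 × 174.4 × 1.45/10 = 50.6, so 51 practices, as stated.
- m = 8: design effect 1.35; 2 × 174.4 × 1.35/8 = 58.9, so 59 practices, as stated.

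A one-sided 0.05 test needs 137.4 per arm, which gives about 40 and 46-47 practices and does not match. The plan therefore implies a two-sided 0.05 test, all of it spent on PACIC.

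**2. Error rate if any one of three tests suffices.** Each test is two-sided at 0.05, so 0.025 lies in the direction favouring tailoring.

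- Any false difference, independent outcomes: 1 − 0.95³ = 14.3%. Ceiling under any dependence: 3 × 0.05 = 15%.
- False result favouring tailoring, independent outcomes: 1 − 0.975³ = 7.3%. Ceiling: 3 × 0.025 = 7.5%.

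The article gives no correlations between the outcomes. For assumed equal correlations, by numerical integration over three normal test statistics:

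| Correlation | Any false difference | False result favouring tailoring |
|---|---|---|
| 0 | 14.3% | 7.3% |
| 0.3 | 13.6% | 6.8% |
| 0.5 | 12.5% | 6.3% |
| 0.7 | 10.9% | 5.5% |
| One outcome only | 5% | 2.5% |

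**3. What an equal alpha split would cost.** Effective patients per arm with 60 practices: 60 × 8/1.35/2 = 177.8, or 60 × 10/1.45/2 = 206.9. Power is Φ(0.3 × √(n/2) − critical value), with critical value 1.960 at 0.05 and 2.394 at 0.05/3.

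| Patients per practice | PACIC power at 0.05 | PACIC power at 0.05/3 |
|---|---|---|
| 8 | Φ(2.828 − 1.960) = 80.7% | Φ(2.828 − 2.394) = 66.8% |
| 10 | Φ(3.051 − 1.960) = 86.2% | Φ(3.051 − 2.394) = 74.5% |

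To keep 80% power after the split, PACIC would need 233 patients per arm before clustering: 2 × 233 × 1.45/10 = 67.6, so 68 practices of 10, or 2 × 233 × 1.35/8 = 78.6, so 79 practices of 8. Both exceed 60.

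**4. If all three had to be significant.** The chance of a false claim for tailoring would be at most 2.5%. Power could not exceed that of the weakest outcome, and for two of the three no power is given.

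**The case against.** **A tempting stronger reading of the number.** A reader might infer that the chance of a false claim for tailoring is 14%. The document does not support that. The null hypothesis is worded in one direction, and the stated sample size fits only two-sided tests. The 14.3% therefore also counts false results favouring standardised delivery, which nobody would present as success for tailoring. For tailoring the figure is about 7%.

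**The success rule is not stated.** A reader might also infer that the plan lets any one positive outcome carry the claim. The Data analysis section says only that the primary outcomes are compared. If all three were required, there would be no inflation. If each were reported as its own claim, each would keep its own 5% rate; the Outcomes section does describe three distinct aspects, and whether these need joint error control can be debated. This stands, so the error rates are conditional.

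**The family may be smaller.** If EQ-5D does not test a null hypothesis about implementation, two outcomes remain. With independence the rates are then 1 − 0.95² = 9.75% and 1 − 0.975² = 4.9%. This is a fair reading, but the text gives EQ-5D the same rank as the others, so which outcomes decide remains open.

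**Multiplicity rules are often left to the analysis plan.** That is true, and one may exist. A reader should not infer that no rule was ever written. But the number of primary outcomes, the single null hypothesis, and the alpha and power basis are fixed in this article. An equal split adopted later would cost power that the stated size does not provide.

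**GAI is closer to the null hypothesis than PACIC.** This also stands. It counts against testing PACIC first, and it has to be weighed against the fact that only PACIC has a sample size behind it.

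**Conclusion.** The point holds in conditional form. The article gives three outcomes equal primary rank, but its alpha and sample size are consistent only with a decision led by PACIC, and nothing says which result rejects the null hypothesis.

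If one significant outcome is taken as enough, the chance of any false difference is about 14% (11-14% for assumed correlations of 0.7 to 0.3; ceiling 15%) instead of 5%. The chance of a false claim favouring tailoring is about 7% (5.5-7%; ceiling 7.5%) instead of 2.5%. These figures assume two-sided 0.05 tests, inferred from the stated practice numbers, and all three null hypotheses true. The power figures also assume 1:1 allocation and one practice per GP.

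The trial remains interpretable. The rule should be settled before the data are seen.

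**What to change.** Before outcome data are seen, name PACIC as the single primary outcome, tested at two-sided 0.05. Then test GAI, the outcome closest to the null hypothesis, and last the EQ-5D utility, each at two-sided 0.05 and each confirmatory only if the one before it is significant. Otherwise report estimates with confidence intervals and make no confirmatory claim. State in the Objectives or Data analysis section that PACIC decides the main comparison, and that EQ-5D is a patient outcome and not a measure of guideline implementation.

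This keeps the family-wise error at 5% and leaves the stated sample size valid, with PACIC power of 81-86% at 60 practices. It needs changes of wording only.

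The cost is that GAI and EQ-5D support no confirmatory claim unless PACIC is positive. For GAI this is a real loss, given how directly it measures guideline adherence, and the investigators should accept it knowingly.
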